#### Children and their parents or caregivers

The study population consists of parents or caregivers of toddlers (one per family). They are included in the study when their child is 5-8 months old and measurements continue until the child is circa 17 months old. Parents of children in the age range of this study have a high attendance percentage (90%) at Child Health Clinics [15].

Only parents who understand the Dutch language and have access to the internet are eligible to be included in the study. The study design and participant flow are shown in Figure 1.

**Figure 1 F1:**
[figure not shown]
**Flow chart of the participants and allocation through the trial**.

### Intervention

The BeSAFE intervention aims at 4 major topics on safety in or around the home of children aged 12 to 24 months; prevention of falling, poisoning, drowning and burning [5,8,16-22]. The different components of the safety topics of the intervention can be found in table 2. The intervention is based on the social ecological model, where safety and health are influenced by a combination of environment (in and around the home) and personal factors (the parents) and the interaction between them [23]. Parents are the most important mediators of the environment of these young and vulnerable children. Parents influence both the physical environment as the social environment of the child, mediated by the parenting style and specific parenting practices [24-27]. Therefore interventions should be aimed at the parents to guarantee the safety and health of the young child. Determinants of parents' behaviours can be found in the Protection Motivation Theory (PMT) and the theory of planned behaviour and includes severity, vulnerability, response efficacy, self efficacy and intentions [10,12-14].

**Table 2 T2:** Safety advices of the intervention based on safety behaviour in and around the home

Safety behaviour concerning the prevention of	Applicable if:	Reinforcement or NO information when:
**Falling**		
- Stair gate	- The house has a staircase which the child can reach	- A stair gate is present en is being used at all times
- Balcony	- The house has a balcony	- The child is never left alone on the balcony
		
**Poisoning**		
- Cleaning products	- Always	- Stored in a closet with a lock or higher than 1.50 meters
- Medicines	- Always	- Stored in a closet with a lock or higher than 1.50 meters
		
**Drowning**		
- Bath tub	- The child takes a bath	- Never left alone in the bath tub
- Swimming pool	- The child swims in the swimming pool	- Never left alone in the swimming pool
- Pond	- There is a pond in the garden	- Always the information to fill up the pond
		
**Burns**		
- Thermostat-controlled tap	- Always	- Thermostat-controlled tap present
- Hot drinks	- Always	- Child never on parents womb when drinking hot drinks
- Kitchen	- Always	- Child never in the kitchen when cooking

The BeSAFE intervention consists of internet-based, tailored safety information combined with personal counselling at the CHC. The BeSAFE intervention module consists of a questionnaire assessing ten specific parents' child safety behaviours in the prevention of falling, poisoning, drowning and burning and determinants of safety behaviour (intentions, possible barriers and self efficacy); a library of safety messages; and algorithm to compose tailored health information for the parent [28]. Parents who give informed consent and fill in the baseline questionnaire receive an e-mail, when their child is about 10 months old, inviting them to participate in the BeSAFE intervention. As a first step parents complete a questionnaire, which is used to generate an online tailored safety advice. When parents have read their personal advice, they are invited to devise and inscribe an implementation intention. In this implementation intention parents plan specific actions for improving their safety behaviour and implementing them in their home situation at a specified time [29,30]. It consists of three parts, i.e. what, when and where. The safety information and implementation intention of each parent will be sent by e-mail to both the parent and the CHC professional, in order to prepare them for the well-child visit at 11 months. At the well-child visit the CHC professional will discuss the safety information and the implementation intention with the parent, using the techniques of motivational interviewing (MI). Motivational interviewing is believed to represent a brief and effective method for addressing behaviour change. Positive attitudes and experienced barriers of the parents are discussed in order to improve parents' child safety behaviours. One aspect of this motivational interviewing is giving attention to transforming positive intention into real behaviour [29-31]. CHC professionals were trained to apply motivational interviewing. Approximately four weeks after the well-child visit parents receive a reminder of their safety information and the implementation intention in order to strengthen the message.

### Control

The control group will receive care us usual; i.e. parents receive a Safety Information Leaflet (for children aged 12-24 months) of the Consumer Safety Institute during their CHC visit at the child age of approximately 11 months [6,21,22,32]. The Safety Information Leaflets contain relevant information about the prevention of injuries of toddlers in or around the home, divided in general information and safety advices about the prevention of falling (i.e. window protection, stair gates, practice walking down the stairs), poisoning (i.e. safe storage of cleaning products and medicines), drowning (i.e. ponds) and burning (i.e. hot fluids, hot pans) [22].

## Measurements

### Primary outcome measures

The primary outcomes of the study are parents' child safety behaviours measured at the child's age of 17 months, regarding the prevention of falling, poisoning, drowning and burning, i.e. presence and use of stair gates, never leaving the child alone on the balcony, safe storage of cleaning products and medicines, never leaving the child alone in the bath tub, safety of a swimming pool or a pond in the garden, thermostat controlled taps, drinking hot fluids while the child is on the parent's lap and keeping the child out of the kitchen while the parents is cooking. In the questionnaires parents are asked which safety behaviours they take in their homes. Some behaviours are only assessed when they are applicable to the situation of the parent. For example, when there are no stairs in the homes, no questions about installing stair gates will be asked.

Presence of safety measures, i.e. stair gate or thermostatic controlled taps is defined as present/not present. Safety behaviour, i.e. closing the stair gate, storing cleaning products after use and drinking hot fluids with a child on parent's lap is scored on a five-point scale from 'never' to 'always'.

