### Follow-up questionnaire

When the child is approximately 17 months old, 6 months after the intervention, all participating parents will receive a follow-up questionnaire. This questionnaire contains the same items on safety behaviours and the determinants of these safety behaviours.

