#### Effect-evaluation

The aim of the study is to assess the effect of internet-based, tailored safety information combined with personal counselling on parents' child safety behaviours. An intention-to-treat analysis will be applied [34]. Regression analysis will be used to evaluate continuous outcome (sum scores) variables, with group (intervention or control group) as independent variable and the baseline values as covariates. Logistic regression analysis will be performed for the evaluation of dichotomous outcomes. Additionally effect modification by composition of the family (one versus two children), educational level and ethnicity of the parents will be explored.

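### Pond item: following the module's advice to fill the pond appears to take the family out of the 17-month comparison, so the analysis of that item would not be intention-to-treat

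*Protocol article*

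**What the plan says.** Under Primary outcome measures, the protocol article states: "The primary outcomes of the study are parents' child safety behaviours measured at the child's age of 17 months". The list that follows includes the safety of a pond in the garden. The same section sets the rule for the questionnaires: "Some behaviours are only assessed when they are applicable to the situation of the parent". Its one example is structural: "when there are no stairs in the homes, no questions about installing stair gates will be asked".

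Table 2, under Drowning, makes the pond topic applicable on this condition: "There is a pond in the garden". The column for states in which the module only reinforces, or says nothing, holds no such state for the pond. The entry reads: "Always the information to fill up the pond".

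On the 17-month measurement, the Follow-up questionnaire section says: "This questionnaire contains the same items on safety behaviours". Effect-evaluation announces an intention-to-treat analysis and adds: "Logistic regression analysis will be performed for the evaluation of dichotomous outcomes". It does not say which families enter the model for a conditional item, or how a hazard that has been removed is scored.

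**The concern.** For most items, safe behaviour leaves the question in place: a family that fits a stair gate still has stairs. For the pond, the advised action abolishes the condition for asking. If applicability is decided afresh at 17 months, membership of the compared group is settled after randomisation and altered by the intervention. The families who responded most fully are missing from the comparison, and more of them from the intervention arm if the module works better than the leaflet. Randomisation no longer protects the contrast between those who remain, and the intention-to-treat label does not restore that protection. At stake is the reading of one declared primary behaviour, and one of the ten points in the sum score if the same scoring feeds into it.

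**Working it through.** **Figures in the plan.** There is none to reproduce on this point. Power of the study gives rates only for stair gates and cleaning products. Pond ownership, filling rates and the safety of retained ponds are not given, so all rates below are assumptions. I also assume that a retained pond can be scored safe in some way and that the advice has no other effect on owners who keep the pond.

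**Main case.** Let s = 0.70 be the proportion of baseline pond owners who are otherwise safe. The proportion who remove the pond is r = 0.20 (intervention) and 0.05 (control). Two analyses are compared:
- A, only families who still have a pond: (safe families remaining) / (1 - r)
- B, all baseline owners, with a removed pond counted as safe

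*Removers are a random mix.*
- A: 70% in both arms, difference 0.
- B: 0.70 + 0.30 x 0.20 = 0.760 versus 0.70 + 0.30 x 0.05 = 0.715, difference +4.5 points.

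*All removers were otherwise safe.*
- A: (0.70 - 0.20)/0.80 = 0.625 versus (0.70 - 0.05)/0.95 = 0.684, difference -5.9 points.
- B: 0.70 in both arms, difference 0.

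*All removers were otherwise unsafe.*
- A: 0.70/0.80 = 0.875 versus 0.70/0.95 = 0.737, difference +13.8 points.
- B: 0.70 + 0.20 = 0.90 versus 0.70 + 0.05 = 0.75, difference +15 points.

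| Who removes the pond | A: still has a pond | B: all baseline owners |
|---|---|---|
| Random mix | 0 | +4.5 |
| All otherwise safe | -5.9 | 0 |
| All otherwise unsafe | +13.8 | +15 |

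**Intermediate cases.** Now take s = 0.30 to 0.50, with filling by 5% of control and 25% to 40% of intervention owners. Let k be how many times as likely an otherwise-safe owner is to fill as an otherwise-unsafe one. The filling rate among unsafe owners is f/(sk + 1 - s), and among safe owners k times that. The odds ratio (OR) for being safe under A is then:
- k = 1: 1.00
- k = 1.5 to 2: 0.58 to 0.89, apparent harm
- k = 0.5: 1.17 to 1.52, a weakened benefit

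Under B the OR is 1.31 to 3.28 across the whole grid.

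**Numbers asked.** If 10% of families had a pond (assumed), the planned 420 completers per arm would include 42 owners each. Under A, about 40 control and 25 to 32 intervention families would still be asked.

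**Which items share the mechanism.** In Table 2, five of the ten items always apply: cleaning products, medicines, thermostat tap, hot drinks and kitchen. Stairs and balcony are features of the house. The bath item depends on the child taking a bath, which the advice does not seek to end. The pool item depends on a condition that parents can change ("The child swims in the swimming pool"), but Table 2 does not advise ending swimming. Only the pond has advice that removes its own condition.

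**The case against.** The strongest reply is that the document does not state the analysis criticised here. Effect-evaluation gives no denominator, the two dichotomous outcomes named in the power section are stair gates and cleaning products, and the sum score comes first in both sections. Table 2 governs which advice is issued and is not itself a scoring rule. The questionnaire is not shown and may record a filled pond as safe. Item-level analysis sets are usually left to a statistical analysis plan.

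Part of this stands. The 17-month denominator is an inference and must be labelled as one. If the questionnaire already counts a filled pond as safe, a clarifying sentence settles the matter. But the article does state the applicability rule, the repetition of items, the advice and the intention-to-treat principle. Read together they conflict for the pond, so this is more than an omitted detail.

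The control leaflet also covers ponds, so only the difference in removal between arms drives the distortion. That is correct, but such a difference is what the intervention sets out to produce.

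A reader might infer that all item-level models are compromised, or that the pond item cannot show a benefit. The documents support neither. Most items lack the mechanism, including the two with power statements, and the otherwise-unsafe case above shows a benefit close to the true one.

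**Conclusion.** The point holds for the pond item, and only possibly for the pool. On the natural reading, comparing families who still have a pond at 17 months conditions on an effect of the intervention and is not intention-to-treat.

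The direction of the error is not fixed: it depends on who fills the pond. Under the assumed 70% otherwise safe and 20% versus 5% removal, the comparison can miss a 4.5-point benefit, show 5.9 points of harm where the scored effect is zero, or understate 15 points as 13.8. The 5.9-point reversal is one extreme, in which every remover was already safe. It should not be quoted as the expected bias, nor as a real benefit turned into harm.

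The mechanism follows from the text on that reading; every size rests on rates that the documents do not give. The stair-gate and cleaning-product comparisons in the power section are essentially untouched.

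**What to change.** In Effect-evaluation, add a rule for the pond item:
- Analyse it in all randomised parents, in both arms, who reported a pond at baseline.
- Score a pond that is gone or filled at 17 months as safe.
- Use the same scoring for the pond point in the 0-10 sum score.
- Keep the comparison among families who still have a pond as a sensitivity analysis.

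Do not extend baseline-fixed applicability to the other conditional items. Baseline is at 5-8 months, and a stair or pool hazard may arise only later. Fixing those sets at baseline could exclude families for whom the item properly applies at 17 months.

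The cost is wording. The baseline questionnaire precedes randomisation and already covers pond safety, so no new data collection appears to be needed. There are two small downsides: ponds acquired after baseline fall outside the main pond analysis, and a house move counts as removal in both arms.

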### Secondary outcome measures

The secondary outcomes are the determinants of the above mentioned parents' child safety behaviours, i.e. severity, vulnerability, response efficacy, self efficacy and intentions. Secondary outcomes, except intentions, are measured on five-point Likert scales.

Severity is measured with one item per safety measure, asking how seriously they perceived the consequences of this event (from not serious at all to very serious). Vulnerability is measured by asking respondents their perception of their child's risk of an unintentional injury on each specific subject (from low risk to high risk).

Response efficacy is assessed by asking how helpful parents perceived the specific behaviour to be for preventing an injury (from very helpful to not very helpful).

Self efficacy is measured by asking parents how difficult or easy they perceive taking the safety measures to be (from very easy to very difficult).

Intentions are assessed by asking whether the parent intends to take the specific safety measure. Answers to be given are yes, within one month; yes, within one to six months, yes, but not within six months; or no intention.

### Baseline questionnaire

The baseline questionnaire, completed at child age of circa 7, 5 months, consists of questions on pregnancy, birth, gender, ethnicity of the child and the parents, educational level of the parents, household and family composition, the ten specific parents' child safety behaviours (presence and use of stair gates, never leaving the child alone on the balcony, safe storage of cleaning products and medicines, never leaving the child alone in the bath tub, safety of a swimming pool or a pond in the garden, thermostat controlled taps, drinking hot fluids while the child is on the parent's lap and keeping the child out of the kitchen while the parents is cooking) and the determinants of these safety behaviours (severity, vulnerability, response efficacy, self efficacy and intentions).

### Follow-up questionnaire

When the child is approximately 17 months old, 6 months after the intervention, all participating parents will receive a follow-up questionnaire. This questionnaire contains the same items on safety behaviours and the determinants of these safety behaviours.

### Process-evaluation

In addition to the effect-evaluation a process-evaluation will be carried out. All parents who use the BeSAFE intervention module are asked to answer a few evaluating questions about the programme, i.e. which part of the advice parents have read, what there opinion is about the advice, do parents intend to change anything in there behaviour after reading the advice and what they think about the time they needed to complete the module. All parents in the intervention group and CHC professionals who provide the intervention will be asked to complete a process-evaluation form after the well-child visit at 11 months where the tailored safety information is discussed. It consists of questions regarding the feasibility of the intervention within the well-child visit, the perceived usefulness of the intervention and the discussed items during the well-child visit.

### Power of the study

We will calculate sum scores of parents' child safety behaviours (0-10 points) of all participating parents, at follow-up as well as at baseline. Power calculations showed that a total number of 1200 parents are needed to detect a difference of 0.34 points between intervention and control group, assuming a mean score of 3.5 points and a standard deviation of 1.7 points, with a power of 0.80 and alpha 0.05. Assuming a participation of 50% and a loss-to-follow-up of 30%, we will have complete data at follow-up form 840 parents (420 in both the intervention and control group).

Considering the dichotomous outcome measures of 'stair gate present' we assume an unsafe situation in 30% of families in the control group [8]. A difference of 9% between the percentages unsafe families of the intervention group and the control group can be shown (21% in the intervention group, 30% in the control group).

Considering the dichotomous outcome measures of 'safe storage of cleaning products' we assume an unsafe situation in 20% of families in the control group [33]. A difference of 8% between the percentages unsafe families of the intervention group and the control group can be shown (12% in the intervention group, 20% in the control group).

### Statistical analyses

Statistical analyses are performed using SPSS 16.0 (SPSS Inc., Chigaco, IL.)

Descriptive statistics are used to describe parents and child characteristics and variable scores (behaviours) for the intervention and control group at baseline and follow-up.

#### Effect-evaluation

The aim of the study is to assess the effect of internet-based, tailored safety information combined with personal counselling on parents' child safety behaviours. An intention-to-treat analysis will be applied [34]. Regression analysis will be used to evaluate continuous outcome (sum scores) variables, with group (intervention or control group) as independent variable and the baseline values as covariates. Logistic regression analysis will be performed for the evaluation of dichotomous outcomes. Additionally effect modification by composition of the family (one versus two children), educational level and ethnicity of the parents will be explored.

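### Optional efficiency gain: the sum-score model could take parental education and family composition, collected before randomisation, as prespecified main-effect covariates

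*Protocol article*

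**What the plan says.** The Protocol article, Power of the study, defines the outcome on which the trial is sized: "We will calculate sum scores of parents' child safety behaviours (0-10 points) of all participating parents, at follow-up as well as at baseline". The sample size is stated as "a total number of 1200 parents are needed to detect a difference of 0.34 points between intervention and control group". The inputs behind that number are a mean of 3.5, an SD of 1.7, power 0.80 and alpha 0.05. With "a loss-to-follow-up of 30" per cent, 840 completers are expected, 420 per arm.

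The Effect-evaluation section gives the model for the sum score: regression "with group (intervention or control group) as independent variable and the baseline values as covariates". It does not say which baseline values are meant; the natural reading is the baseline sum score. The same section then names family composition (one versus two children), educational level and ethnicity, but only as effect modifiers to be explored.

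The Baseline questionnaire section shows that these variables are at hand. The list includes "educational level of the parents, household and family composition", together with ethnicity, the ten behaviours and their determinants. Table 1 places this questionnaire before randomisation in both arms.

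**The concern.** In a randomised comparison of a continuous score, adjusting for baseline variables that predict the outcome reduces residual variance and narrows the interval for the group difference. In a linear model it does so without changing what is being estimated. The trial already holds such candidates, measured before allocation, so adjustment cannot condition on anything the intervention has altered. The plan thinks education and family composition relevant enough to examine for effect modification, yet does not enter them as main effects in the main analysis.

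At stake is a modest amount of precision that would cost almost nothing to obtain. There are two lesser benefits. A list fixed in advance rules out choosing covariates by significance once the data are seen. And with 30% loss expected, an analysis of completers is easier to defend if it includes variables that predict both dropout and outcome, should these prove to do so.

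**Working it through.** **Inputs from the article (Power of the study).** Difference 0.34, SD 1.7, power 0.80, alpha 0.05, loss 30%, 1200 recruited, 840 completers (420 per arm). Sidedness is not stated; two-sided is assumed.

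**Inputs not in the article.** The baseline-outcome correlation (rho) and the share of the remaining variance explained by added covariates (R²). Both are assumed below: rho 0.2 to 0.6, R² 1% to 10%.

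**Step 1: the plan's own figure.**
- n per arm = 2 × (1.960 + 0.842)² × (1.7/0.34)² = 2 × 7.849 × 25 = 392.4, so 393 per arm and 786 completers.
- With 30% loss: 786/0.70 = 1123, against 1200 stated. The stated number is not reproduced exactly but errs on the generous side. (One-sided testing would give 310 per arm, further away.)
- 1200 × 0.70 = 840, as stated.

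**Step 2: power with no covariate at all.**
- SE = 1.7 × √(2/420) = 0.1173.
- Power for 0.34 = Φ(0.34/0.1173 − 1.960) = 0.826.
- Detectable difference at 80% power = 2.8016 × 0.1173 = 0.329.

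The sample size therefore takes no credit for covariate adjustment and still exceeds 0.80.

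**Step 3: power with covariates.** Residual SD = 1.7 × √[(1 − rho²)(1 − R²)], 420 per arm, difference 0.34:

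| rho | baseline score only | + R² 1% | + R² 5% | + R² 10% |
|---|---|---|---|---|
| 0.2 | 0.841 | 0.845 | 0.859 | 0.877 |
| 0.4 | 0.885 | 0.888 | 0.901 | 0.915 |
| 0.6 | 0.952 | 0.954 | 0.961 | 0.969 |

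Across this grid the added covariates raise power by about 0.2 to 3.6 percentage points.

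**Step 4: interval width and equivalent completers.** Neither depends on rho.
- Interval narrowing = 1 − √(1 − R²): 0.5% at 1%, 2.5% at 5%, 5.1% at 10%.
- Extra completers = 840/(1 − R²) − 840: 8 at 1%, 44 at 5%, 93 at 10%.

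**Step 5: cost if nothing is explained.** Two covariates use a few degrees of freedom out of about 838, which is negligible.

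**The case against.** The strongest reply is that nothing here is wrong. Regression of the follow-up score on group and baseline score is a standard, prespecified and unbiased analysis of a randomised trial, and the trial does not rely on any further precision. A condensed article may also leave the exact covariate list to a fuller document, and the undefined plural in the model sentence could be meant more widely. All of this stands, and it is why the point is optional. It does not remove the point, because the article itself assigns education and family composition an exploratory role only.

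Three stronger readings are tempting and not supported.

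- A reader might infer that the baseline score must be a weak covariate, because it is taken at 5-8 months and the outcome at 17 months, a gap of 9 to 12 months. Table 2 does make the stair gate conditional: "The house has a staircase which the child can reach". But that column governs when advice is given, and five of the ten rows (cleaning products, medicines, thermostat tap, hot drinks, kitchen) apply always. The article reports no correlation. Even a weak baseline covariate leaves the model valid.
- A reader might infer a gain of 100 to 170 completers. That needs rho = 0.4 (16% explained) and a rise to 25% or 30%: 840 × 0.84/0.75 = 941, or 840 × 0.84/0.70 = 1008. The added variables would have to explain 0.09/0.84 = 11% to 0.14/0.84 = 17% of the residual variance. The document gives no basis for that.
- A reader might want the behavioural determinants in the model, since the Intervention section draws on "the theory of planned behaviour and includes severity, vulnerability, response efficacy, self efficacy and intentions". But the article measures these per behaviour, asks some behaviours only where applicable, and defines no single self-efficacy score or intention stage. They are not ready for use as covariates.

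**Conclusion.** The point holds as an optional improvement in efficiency. The planned sum-score model is valid and, at 0.826 unadjusted against the stated 0.80, adequately powered on the article's own figures. It would be wrong to call it biased, underpowered or mistaken.

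What remains is that variables with a plausible prognostic role, already collected before randomisation, are left out of the main model. The size of the benefit rests wholly on an assumption: with 1% to 10% of residual variance explained, the gain runs from trivial to modest, and with none explained the loss is negligible. The conclusion is confined to the linear model for the sum score and does not extend to the logistic analyses.

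**What to change.** In the Effect-evaluation section, or in the analysis plan if one exists:

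- State that the baseline values in the sum-score model mean the baseline sum score.
- Prespecify parental educational level and family composition (one versus two children) as further main-effect covariates in the main sum-score model, with their categories fixed beforehand and no selection by significance.
- Keep the model with group and baseline sum score only as a sensitivity analysis.
- Add baseline determinants such as self efficacy only if a single score, with a rule for non-applicable items, is defined beforehand.

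The exploratory effect-modification analyses can stay as they are. The cost is a sentence or two of text and a few degrees of freedom. No new data are needed, and neither the sample size nor trial conduct changes.
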